### Randomization

The blocked randomization, stratified by study center and gender of patients, will be performed centrally when CR or LDA is achieved (V0, week 0). The staffs responsible for randomization will obtain the group allocation code from the Peking University Clinical Research Institute (PUCRI) through an Interactive Web Response System (IWRS).

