### Study outcomes

The primary outcome will be disease relapse, which is defined as DAS28-CRP increases by at least 0.6 compared with that at randomization and is greater than 3.2 simultaneously.

The secondary outcomes will include the following: the incremental cost per reducing 1 case of relapse; change of disease activity score from baseline, assessed by DAS28-CRP, DAS28-ESR, CDAI and SDAI, at 60 weeks after randomization; duration of maintaining CR or LDA after randomization; change of hands X ray modified Sharp score at 60 weeks after randomization; ultrasound remission of hands at 60 weeks after randomization; Health Assessment Questionnaire Disability Index (HAQ-DI) and health related quality of life [the five-levele EuroQol-5D-5L (EQ-5D-5L) and short form-6D (SF-6D)] at 60 weeks after randomization; adverse events and complications; and patient reported outcomes (PRO) including rash, nausea, vomiting, diarrhea, abdominal pain and fever.

All outcomes will be measured after 60 weeks.

Responsible physicians will monitor and record any adverse events (AEs) during the whole trial. Expected AEs will include: allergy; ALT and AST elevation; hemocytopenia; infection; digestive tract symptom including nausea and vomiting; and hemorrhage of digestive tract defined by fecal occult blood positive, etc. In case of AEs, symptomatic treatment or reduction of drug dosage or even discontinuation of drugs will be carried out when necessary. If the drugs is tapered or discontinued, a serious AE will be considered and the patient should exit the study. Physicians will assess the association between intervention and AEs on a 6-point scale (1 = definitely related; 2 = probably related; 3 = possibly related; 4 = probably not related; 5 = definitely not related; 6 = unknown). All AEs will be categorized into three levels using the Spilker classification [(1) mild = not need additional intervention, nor significantly inhibit normal life function of the participant; (2) moderate = significantly inhibit the normal life function of the participant, and may need additional intervention, recovering afterwards; and (3) severe = require intensive intervention, and leave sequelae).

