#### Sample size estimation

According to the study purposes, a superiority design was considered appropriate. Our hypothesis is that the relapse rate in group A (triple therapy group) will be lower than that in group C (MTX monotherapy group) in 60 weeks after randomization.

Sample size was calculated by PASS 11.0. It was reported that for patients with established RA achieving CR or LDA by TNFi combined with MTX, 24% to 85% suffered from disease relapse after discontinuation of TNFi [4–7]. When combined csDMARDs preserved after TNFi removed, the rate of relapse was 51.2–58% [4, 7]. We assume that adding HCQ + SSZ 3 months before the removal of TNFi may somehow decrease the relapse. Accordingly, we expect the relapse rate as 50% in patients in triple therapy group, and 74% in MTX monotherapy group. With a power of 0.8 and a significance level of 0.05 (two-sides), using a 1:1:1 treatment allocation of enrollment, to detect the difference of relapse rate between the two groups, the required sample size is 61 for each group. Given the estimated dropout rate of 20%, we intend to recruit a total of 240 subjects (80 for each group).

We assume that the relapse rate may be similar between group A and group B (TNFi maintenance therapy group), and the cost-effectiveness may be better in group A than in group B. The relapse rate and cost-effective comparison between group A and group B will be exploratory and there was no relevant research hypothesis, so the sample size was not calculated by it.

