#### Statistical analysis

All statistical analyses will be performed using SAS 9.2.

The compatibility of baseline data among three groups will be checked. Student’s t-test or Wilcoxon rank sum test will be used for quantitative variables. Chi-square test or Fisher’s exact test will be used for categorical variables. The Cochran–Mantel– Haenszel test or the Wilcoxon rank sum test will be used for ordinal variables.

To compare the relapse rate between triple therapy group and MTX monotherapy group, the intention-to-treat principle will be followed. Considering the influence of central effect, the collected data will be estimated by mantel Haenszel method with stratification by study centers. Kaplan–Meier curves will be used to show the differences of relapse rate among three groups. The disease activity changes and other continuous secondary outcomes (Sharp score, ultrasonic Doppler score and HAQ-DI score) will be compared between the study groups using the covariance analysis model. Per protocol analyses will also be conducted as sensitivity analyses.

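### Randomisation is stratified by centre and gender but the primary Mantel-Haenszel analysis by centre only, which makes the test mildly conservative if gender predicts relapse

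*Protocol article*

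**What the plan says.** Under Randomization, the protocol article states: "The blocked randomization, stratified by study center and gender of patients, will be performed centrally". Gender is therefore known for every patient when treatment is allocated.

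Under Statistical analysis, the primary comparison is set out as: "To compare the relapse rate between triple therapy group and MTX monotherapy group, the intention-to-treat principle will be followed". The method follows at once: "Considering the influence of central effect", "the collected data will be estimated by mantel Haenszel method with stratification by study centers". The centre effect is the only reason offered for stratifying. Gender does not appear in that section, and the article does not say why it is left out.

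The primary outcome is binary (relapse yes or no). The article names the strata of the primary analysis outright, so this is a stated rule rather than a detail left to a later plan.

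**The concern.** Blocking within gender keeps the proportions of men and women close to equal in groups A and C. If relapse risk differs between men and women, this takes one source of chance variation out of the A minus C difference. A variance estimated by centre alone still counts that source. The interval is then wider than it needs to be, and the test rejects less often than its nominal 5%.

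At stake is a little precision in the one comparison the trial is powered for. The information needed to recover it is already collected.

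**Working it through.** **Inputs from the protocol.** Sample size estimation: "we expect the relapse rate as 50% in patients in triple therapy group, and 74% in MTX monotherapy group"; power 0.8; two-sided 5% level; 61 per group; 20% dropout; 80 per group and 240 in total. Eligibility criteria: seven centres. Trial status: 123 randomised so far.

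**Assumptions, because the documents are silent.** Share of men 20% or 50%; a gender gap in relapse of 0 to 30 percentage points, the same in both arms; outcome known for all 80 per arm. The article does not name the Mantel-Haenszel effect measure. The figures below are for the risk difference and the Cochran-Mantel-Haenszel test.

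**Step 1: the plan's own figure.** With V = 0.50 × 0.50 + 0.74 × 0.26 = 0.4424,

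n = (1.960 + 0.842)² × V / 0.24² = 7.849 × 0.4424 / 0.0576 = 60.28, rounded up to 61. This matches the protocol. Then 61 / 0.8 = 76.25, so 77 per group, and the planned 80 covers it.

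**Step 2: how much too wide.** With f the share of women and g the gender gap, gender contributes f(1−f)g² to the outcome variance in each arm. Balance on gender removes 2f(1−f)g² from V, while the centre-only standard error keeps it:

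ratio of standard errors = √[V / (V − 2f(1−f)g²)].

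For 20% men and 20 points: 2 × 0.8 × 0.2 × 0.04 = 0.0128, and √(0.4424 / 0.4296) = 1.015. The table sets the formula beside a simulation of 40,000 trials per scenario (80 per arm, seven equal centres without a centre effect, near-perfect balance within centre and gender). Each pair reads centre only / centre and gender. Type I error is at 74% in both arms; standard error and power are at 50% against 74%.

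| Men | Gap (points) | Formula ratio | Standard error | Type I error, % | Power, % |
|---|---|---|---|---|---|
| 20% | 0 | 1.000 | 0.0739 / 0.0741 | 5.0 / 5.1 | 88.5 / 88.4 |
| 20% | 10 | 1.004 | 0.0739 / 0.0738 | 4.7 / 4.7 | 88.5 / 88.5 |
| 20% | 20 | 1.015 | 0.0739 / 0.0730 | 4.6 / 5.0 | 88.5 / 89.0 |
| 20% | 30 | 1.034 | 0.0739 / 0.0716 | 4.1 / 4.9 | 89.3 / 90.4 |
| 50% | 20 | 1.023 | 0.0739 / 0.0723 | 4.2 / 4.8 | 89.0 / 89.8 |
| 50% | 30 | 1.055 | 0.0738 / 0.0701 | 3.8 / 5.0 | 89.6 / 91.6 |

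In absolute terms, with 20% men and a 30-point gap, the 95% half-width is 1.96 × 0.0739 = 14.5 points by centre and 1.96 × 0.0716 = 14.0 points by both factors.

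**Step 3: how large such a gap is.** With 20% men and 74% relapse overall, a 30-point gap means, for example, 80% in women and 50% in men (0.8 × 80 + 0.2 × 50 = 74), an odds ratio of (80/20) / (50/50) = 4. A 20-point gap means 78% and 58%, an odds ratio of (78/22) / (58/42) = 2.6. These are strong effects.

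**Step 4: a design closer to this trial.** Near-perfect balance could flatter the result, so the check was repeated with three-arm blocks of six and unequal centres (block size and centre shares assumed; two runs, of 8,000 and 2,500 trials per scenario). At 240 randomised and a 30-point gap, the centre-only type I error was 4.1 to 4.3% with 20% men and 3.5 to 3.7% with 50% men, against 4.9 to 5.1% with both factors. In the larger run, power was 89.4% against 90.7%, and 89.6% against 91.6%. The conclusion does not depend on perfect balance.

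**Step 5: the price if gender does not matter.** Centre by gender gives 7 × 2 = 14 strata. Groups A and C together hold 160 patients at 240 randomised. With 20% men that is 160 × 0.2 / 7 = 4.6 men per centre. At 123 randomised it is 82 × 0.2 / 7 = 2.3. Strata with patients from one arm only contribute nothing. With no gender effect, the loss was 0.1 to 0.8 power points at 240. At 123, with 20% men and equal centres, power fell from 60.4% to 58.7% (4,000 trials). The Monte Carlo error of each of these is √(0.6 × 0.4 / 4,000) = 0.8 points, so the loss should be read as about 1 to 2 points.

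**The case against.** The strongest reply is that the harm rests on a condition found nowhere in the documents. No section says that gender predicts relapse or gives the share of men. At a 10-point gap nothing visible happens, and even at 20 points the change is half a power point to one point. The error is on the safe side, and power at 80 per arm is near 88% by either analysis, above the 80% target. A centre-only rule is also simple and fully fixed, whereas 14 strata bring sparse cells for men and a pooling decision. If recruitment stalls near 123, adding gender could lose more than it gains. All of this stands. It makes the point minor and means the change has a cost.

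What remains is that the protocol chose gender as a design factor, fixed an analysis that ignores it, and gives no reason.

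Three stronger readings are tempting and are not supported:

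- A reader might infer that the mismatch inflates the type I error or undermines a positive finding. The calculations show the opposite direction.
- A reader might infer that gender must be prognostic because it was stratified on. The article makes no such claim.
- A reader might extend the criticism to the covariance models for the continuous outcomes. The article lists no covariates for them, which is commonly left to the analysis plan, so no error is stated there.

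**Conclusion.** The mismatch is real and stated in the document, and its consequence is small. If gender predicts relapse, the centre-only primary analysis is mildly conservative. With 20 to 50% men (assumed), the interval is about 1 to 2% too wide at a 20-point gender gap and 3 to 5% at 30 points. The type I error is about 4.2 to 4.6% at 20 points and 3.5 to 4.3% at 30 points. About 0.5 to 2 power points are given away at 240 randomised. If gender is not prognostic there is no harm. The validity of a significant A versus C result is not in question. This is a minor, inexpensive improvement, not a defect that puts the trial's conclusion at risk.

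**What to change.** Before database lock, amend the primary analysis along these lines: *Relapse in groups A and C will be compared by the Mantel-Haenszel method stratified by study centre and gender. Centres with fewer than a stated number of patients in A and C combined will be pooled, using stratum sizes only and without sight of outcomes. The analysis stratified by centre alone will be a sensitivity analysis.* The team should name the pooling threshold now, so that the primary test leaves no choice to the analyst.

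The cost is a short amendment by the route described in the Discussion, with no new data. The statistical price, if gender turns out to have no effect, is under 1 power point at 240 randomised and about 1 to 2 points if recruitment stays near 123. The change should be made while the trial is running, because adding gender after outcomes are known would look data-driven.

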### Exit criteria

Patients or their authorized representative require withdrawal from the study;Do not achieve DAS28-CRP < 3.2 by the end of 12 weeks in the induction treatment;Relapse during the randomized phase;Because of AE or SAE, the responsible physician considers that the patient is not suitable to continue the trial;Because of protocol violation (PV), the responsible physician considers that the patient is not suitable to continue the trial;Become pregnant.

Participants will be advised verbally and in writing that they will be free to withdraw at any stage upon request.

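### Week-60 disease activity is compared by ANCOVA although relapsers exit early; whichever of their scheduled values are used, the A–C contrast for the DAS28 family is distorted

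*Protocol article*

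**What the plan says.** Study outcomes lists "change of disease activity score from baseline, assessed by DAS28-CRP, DAS28-ESR, CDAI and SDAI, at 60 weeks after randomization", gives the same time point for the modified Sharp score, ultrasound remission and HAQ-DI, and adds that every outcome is measured after 60 weeks.

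Statistical analysis names ANCOVA both for change in disease activity and for the remaining continuous measures: "other continuous secondary outcomes (Sharp score, ultrasonic Doppler score and HAQ-DI score) will be compared between the study groups using the covariance analysis model". Its intention-to-treat sentence is attached to the relapse-rate comparison. Nothing is said there about which patients or which values enter the ANCOVA.

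Exit criteria includes "Relapse during the randomized phase". Follow up schedule and data collection sends relapsers to empirical treatment and keeps those who exit under observation for safety and cost-effectiveness; the note to Fig. 1 mentions cost data. Table 1 has an early-exit column that ticks the committee examination, CRP/ESR, hand X-ray, hand ultrasound and HAQ-DI/EQ-5D.

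Sample size estimation states: "we expect the relapse rate as 50% in patients in triple therapy group, and 74% in MTX monotherapy group".

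**The concern.** The outcome time, the exit rule and the named method do not fit together for half of group A and about three quarters of group C. Exit is triggered by a rise in DAS28-CRP, which is itself one of the analysed outcomes. An ANCOVA of values observed at week 60 therefore leaves out most of the patients whose DAS28 rose, and more of them in the arm that does worse. An ANCOVA that takes the early-exit value as final records each relapser near the relapse threshold, at an earlier time, and does so for more patients in C than in A.

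At stake is the secondary evidence on the A–C comparison. A real effect of triple therapy on disease activity could be reported as roughly half its size, in a comparison that a reader would take to be randomised.

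**Working it through.** **1. The plan's own figure.** Inputs from Sample size estimation: relapse 50% and 74%, two-sided 0.05, power 0.80. With unpooled variance:

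n = [0.50×0.50 + 0.74×0.26] × (1.960 + 0.842)² / 0.24² = 60.28, rounded up to 61.

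This agrees with "the required sample size is 61 for each group". Allowing for 20% dropout, 61/0.8 gives 77, within the planned 80. The sample size is not in question; its relapse rates are the inputs for what follows.

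**2. Who has a week-60 value.** Of 80 per arm, before other dropout, 80 × 0.50 = 40 in A and 80 × 0.26 = 20.8, about 21, in C never relapse. Patients who first meet the criterion at the week-60 visit also have week-60 data. Under the simulations in step 4 this gives about 43–46 in A and 25–27 in C.

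**3. The mechanism in its simplest form.** Suppose (an assumption) that DAS28 change is normal with SD σ, and relapse means a change above 0.6. The means that give 50% and 74% relapse are 0.6 and 0.6 + 0.643σ, so the full C–A difference is 0.643σ. The mean among non-relapsers is m − σφ(a)/Φ(a), with a = (0.6 − m)/σ. The subtracted term is 0.798σ in A (a = 0) and 1.248σ in C (a = −0.643). The non-relapser difference is 0.643σ − (1.248 − 0.798)σ, about 0.194σ, or 30% of the full difference. For σ from 0.8 to 1.2, a difference of 0.51–0.77 becomes 0.15–0.23.

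**4. Visit-by-visit simulation.** Assumed, not in the document: baseline mean 2.4, SD 0.6, cut at 3.2; linear drift after week 12 with slope SD 0.8, 1.0 or 1.2; residual SD 0.3, 0.4 or 0.5. Mean slopes are tuned to 50% and 74% relapse by the protocol's definition at its scheduled visits. Ranges are over the three SD sets.

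| Values used | C–A difference in DAS28 change | Share kept (lower and upper ends) |
|---|---|---|
| All randomised, no post-relapse treatment | 0.65–1.05 | reference |
| Everyone with an observed week-60 value | 0.43–0.64 | 0.43/0.65 = 66%; 0.64/1.05 = 61% |
| Non-relapsers only | 0.35–0.52 | 54%; 50% |
| Early-exit value taken as final | 0.37–0.61 | 57%; 58% |
| All visits up to exit, missing at random | 0.65–1.05 | about 100% |

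The second row falls to just over half when the comparison is also adjusted for baseline, as an ANCOVA would be.

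**5. Other assumptions.** With baseline mean 2.5, SD 0.5, slope SD 0.6–1.5 and residual SD 0.3–0.5, the full difference is 0.50–1.03. Non-relapsers keep 37–56% of it (0.28–0.48) and early-exit values 51–61% (0.30–0.57). If relapsers are instead measured at week 60 after effective post-relapse treatment, 0.03–0.34 remains, but that answers a different question.

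**6. Sharp score, ultrasound, HAQ-DI.** These do not define relapse, so the truncation argument does not carry over. Selection could even reverse the sign. As an illustration with assumed values, let C keep its most stable 26% (mean change −0.2), and let A keep a like 26% plus 24% marginal patients (+0.3). Then A averages (26×(−0.2) + 24×0.3)/50 = +0.04 against −0.20 in C, which favours C.

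**The case against.** The strongest reply is that the article never limits the ANCOVA to patients who reach week 60 without relapse. A reader might infer a survivors-only analysis, but the early-exit column gives each relapser a planned value for every named outcome. Patients relapsing at week 60 itself are fully assessed, and the sentence that all outcomes are measured after 60 weeks could be read to cover everyone. This stands: a survivors-only analysis is one possible reading, not the stated plan.

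A second reply is that analysis sets and missing-data rules belong in a statistical analysis plan, which is not shown. This stands as far as the missing rule goes. It does not remove the point, because the time point and the method are fixed here, and both kinds of value in the stated on-study schedule attenuate the DAS28 contrast. Nor can an analysis plan supply week-60 HAQ-DI or imaging in relapsers if these are not collected.

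Third, the simulation favours the proposed model: drift is linear, exit depends only on recorded DAS28, and withdrawals and adverse-event exits are left out. This also stands. The direction for DAS28 is well supported; the exact size is not.

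Two further inferences are not supported. One is that the interval would be falsely narrow: under the step 4 assumptions the 95% half-width is 0.30/0.39/0.48 among non-relapsers against 0.27/0.33/0.40 in all randomised, so it is wider. The other is that all the outcomes are biased towards no difference; step 6 shows why that cannot be said.

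**Conclusion.** The point holds for the DAS28 family. The week-60 definition, the exit at relapse and the ANCOVA conflict, the article leaves open which relapser values are used, and neither scheduled choice gives an undistorted A–C contrast at week 60. The likely effect is attenuation, to the shares given in step 4 and somewhat lower under some of the sets in step 5. These sizes rest on the protocol's relapse rates and on assumed DAS28 means, SDs and drift. Only DAS28-CRP was modelled; DAS28-ESR, CDAI and SDAI are expected to behave similarly as measures of the same disease activity. The reference is the difference without post-relapse treatment.

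For Sharp score, ultrasound and HAQ-DI, only the selection or the unequal timing is established. These are secondary outcomes. The primary comparison counts relapsers as events and is not touched, so this is a needed correction but not one on which the trial's main conclusion depends.

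**What to change.** For DAS28-CRP, DAS28-ESR, CDAI and SDAI, replace the week-60 ANCOVA with a mixed model for repeated measures on all randomised patients by allocated group. Use every scheduled visit up to and including the early-exit visit, with baseline, centre, sex, visit and arm-by-visit terms. Report the week-60 contrast and label it as the effect without post-relapse treatment. The cost is analysis wording only, since Table 1 already schedules the committee examination and CRP/ESR at each randomised-stage visit.

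The downside is reliance on missing at random. That is credible for exit by relapse, because recorded DAS28-CRP triggers it. It is less exact for the three indices that are not the trigger, and less credible for other dropout, so a sensitivity analysis is advisable.

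For Sharp score, ultrasound and HAQ-DI, reconcile Follow up schedule and data collection, Study outcomes and Statistical analysis on which relapser values are analysed, and do not present a comparison of non-relapsers as a randomised comparison. Taking these measures at week 60 in patients who have exited would be a new procedure for them, would estimate an effect that includes post-relapse treatment, and could not recover assessments already missed among the 123 patients randomised so far. If it is chosen, the article should say so.

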**Fig. 1 Fig1:**
[figure not shown]
The study flow chart. Note: for patients who relapse during follow up, the study treatments will be stopped and patients will be referred to appropriate alternative treatments and follow up will be continued for cost data collection. RA: Rheumatoid Arthritis; csDMARDs: conventional synthetic disease-modifying anti-rheumatic drugs; MTX: methotrexate; HCQ: hydroxychloroquine; SSZ: sulfasalazine; TNFi: Tumor necrosis factor α inhibitors; CR:clinical remission; LDA: low disease activity

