### Follow up schedule and data collection

A total of at most 14 visits will be scheduled. Data to be collected at each visit are summarized in Table 1.

**Table 1 Tab1:** Follow up schedule and data to be collected

Study period	Induction treatment stage		Randomized stage										Early exit
Visit	S1	S2-4	V0	V1	V2	V3	V4	V5	V6	V7	V8	V9	
	Wk0	Wk 4\8\12	Wk0	Wk4	Wk8	Wk12	Wk20	Wk28	Wk36	Wk44	Wk52	Wk60	
ICF	√												
Demographic data	√												
Past history and medication history collection	√												
Physical examination	√	√ √	√	√	√	√	√	√	√	√	√	√	√
Urine βHCG (if applicable)	√												
BCC, renal function, liver function, ESR,CRP,RF	√	√	√	√	√	√	√	√	√	√	√	√	√
Assessment committee examination	√	√ √	√	√	√	√	√	√	√	√	√	√	√
IC/EC judgement	√												
Randomization		√											
Hand X-ray-ran	√		√									√	√
Ultrasound of double hands	√		√									√	√
Anti-CCP antibody	√											√	√
Cost of exam and treatment	√		√	√	√	√	√	√	√	√	√	√	√
HAQ-DI/EQ-5D	√		√			√						√	√
Study Medication record	√	√	√	√	√	√	√	√	√	√	√	√	√
Concomitant medication record	√	√ √	√	√	√	√	√	√	√	√	√	√	√
AE record	√	√ √	√	√	√	√	√	√	√	√	√	√	√

*ICF* informed consent form, *BCC* blood cells count, *ESR* erythrocyte sedimentation rate, *CRP* c reactive protein, *RF* rheumatoid factor, *IC/EC* inclusion criteria/exclusion criteria, *Anti-CCP antibody* anti-cyclocitrulline polypeptide antibody, *HAQ-DI/EQ-5D* Health Assessment Questionnaire Disability Index/ Euro Qol five dimensions questionnaire, *AE* adverse event

Patients will be requested to return the residual drugs to obtain new drugs at each visit. Laboratory tests must be performed in the eligible study centers. These strategies were designed to improve adherence of subjects.

Subjects who relapse or cannot tolerant adverse effects before the end of the trial should exit the trial and receive empirical treatment, including but not limited to, other biological agents, or csDMARDs combination therapy. All patients who exit early will be kept in following up for the safety and cost-effectiveness analysis.

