Serious adverse event (SAE) is defined as any of the following conditions: (1) threat to life; (2) lead to hospitalization or extend hospital stay; (3) lead to permanent or notable disability or functional disorder; and (4) lead to taper or discontinue the study drugs. In case of SAE or scheme violation during study duration, the relevant Institutional Review Board (IRB) and the leading study site (Peking University First Hospital) will be informed and will decide whether the trial will continue or not. Patients will be followed even if protocol has been breached for any reason. The SAE will be recorded as safety outcome.

An independent assessment committee will be set up for outcomes evaluation. The assessment committee will be blinded to the treatments. However, in case of “SAE”, unblinding will be permitted.

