Pharmaceutical economics analysis will be performed. Base case analysis and sensitivity analysis will be performed by decision tree model based on Per-Protocol Set (Fig. 2). A series of one-way deterministic sensitivity analysis will be conducted. For the cost-effectiveness analysis, the proportion of not relapse will be taken as effectiveness. The direct cost (medical expenses), indirect cost (productivity lost), total cost (the total of direct and indirect cost), and average cost/effectiveness ratio of each treatment strategy will be calculated. Direct cost will include the cost of experimental drugs, laboratory and radiology examinations, AE/SAE treatment, traffic expenses and accommodation fees directly related with follow-up visit. Indirect cost will include loss of income due to the patients’ and their family’s inability to work due to RA. The incremental cost effectiveness ratio (ICER) of group A and group B against group C will be calculated. Cost-utility analysis will be performed by using EQ-5D-5L and SF-6D as utility index. The costs and average cost/utility ratio of each treatment strategy will be calculated. The incremental cost utility ratio [the cost of increase 1 quality adjusted life year (QALY)] of group A and group B against group C will be calculated. The treatment strategy will be considered to have cost-utility if the incremental cost utility ratio is below 3 times of China’s per capita GDP in the past year (¥100,000).

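### The economic base case and its sensitivity analysis both rest on the Per-Protocol Set, although early exits are followed for cost-effectiveness and relapse is compared by intention to treat

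*Protocol article*

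**What the plan says.** On the economic analysis, the Statistical analysis section states: "Base case analysis and sensitivity analysis will be performed by decision tree model based on Per-Protocol Set (Fig. 2"). Effectiveness is the proportion without relapse, and ICERs of groups A and B against C are planned. Costs of treating adverse events are among the direct costs. No economic analysis in all randomised patients is mentioned.

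Other parts of the article point the other way:

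- Follow up schedule and data collection: "All patients who exit early will be kept in following up for the safety and cost-effectiveness analysis".
- Note to Fig. 1, on patients who relapse: "follow up will be continued for cost data collection".
- Study outcomes: "Patients will be followed even if protocol has been breached for any reason".
- Statistical analysis, on relapse in A versus C: "the intention-to-treat principle will be followed", and then "Per protocol analyses will also be conducted as sensitivity analyses".

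On who leaves early, Follow up schedule and data collection says: "Subjects who relapse or cannot tolerant adverse effects before the end of the trial should exit the trial and receive empirical treatment". Study outcomes adds: "If the drugs is tapered or discontinued, a serious AE will be considered and the patient should exit the study". The article does not define the Per-Protocol Set.

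**The concern.** The trial keeps following early exits for the economic analysis, and then names for that analysis a population that would ordinarily leave some of them out. It also reverses the hierarchy used for relapse: per-protocol supports the clinical comparison but is the sole basis of the economic one.

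Tolerance, adherence and protocol violation all arise after randomisation and can depend on the allocated strategy. Group A alone adds two drugs at randomisation (Interventions), and stopping or tapering a drug leads to exit. If such patients are left out, the groups compared are no longer those that were randomised. The cost of managing their adverse events and of their later treatment also leaves the analysis, although a payer choosing the strategy would bear it.

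Two consequences follow. The effectiveness term in the ICER need not agree with the intention-to-treat relapse result. And the planned bootstrap, one-way and probabilistic analyses cannot reveal the problem if they run on the same selected set. Cost-effectiveness is in the title and the stated aim, and the cost-utility result is to be judged against a threshold of three times per capita GDP.

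**Working it through.** **The plan's own figure.** No stated number depends on the economic population. The relapse rates used below come from Sample size estimation (50% in A, 74% in C, power 0.80, two-sided 0.05), and the size given there reproduces with the unpooled normal approximation:

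n = (1.960 + 0.842)² × (0.50×0.50 + 0.74×0.26) / 0.24² = 60.28, so 61 per group, as stated. Then 61/0.8 = 76.25, so 77, against 80 planned.

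**Must relapsers stay in the Per-Protocol Set?** Relapse is an exit criterion. If every exit were dropped, relapsers included, group A would keep 80 × 0.50 = 40 patients and group C 80 × 0.26 = 20.8, all without relapse. Non-relapse would be 100% in every group, the difference 0, and the ICER undefined. So relapsers have to be retained. The exclusions at issue are protocol violators and, depending on the definition, exits for intolerance, taper or withdrawal.

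**How far could exclusions move the ICER denominator?** Assumptions, for illustration only:

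- 80 patients per group; non-relapse among all randomised is 50% in A (40 of 80) and 26% in C, a difference of 0.24.
- 20% of A (16 of 80) is excluded. The article gives no figure for this.
- Exclusions in C are unrelated to outcome, so C stays at 26%.

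The result depends on how many of the 16 relapsed:

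| Relapsed among the 16 | Non-relapse in A, Per-Protocol Set | A − C | Ratio to 0.24 |
|---|---|---|---|
| none | (40 − 16)/64 = 0.375 | 0.115 | 0.48 |
| half | (40 − 8)/64 = 0.500 | 0.240 | 1.00 |
| all | 40/64 = 0.625 | 0.365 | 1.52 |

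With 10% excluded (8 of 80) the extremes are (40 − 8)/72 = 0.444 and 40/72 = 0.556. The differences are 0.184 and 0.296, or 0.77 and 1.23 times 0.24.

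If the cost difference were unchanged, the ICER would be multiplied by 0.24/0.115 = 2.09 at one extreme of the 20% case and by 0.24/0.365 = 0.66 at the other. The cost difference would move as well, but the article gives no cost data from which to say by how much.

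**Can the fix be carried out with the planned data?** Cost follow-up after exit is already planned. Table 1 schedules HAQ-DI/EQ-5D at S1, V0, week 12, week 60 and early exit, with no explicit schedule after exit. The Fig. 1 note promises follow-up after relapse for costs only. The direct-cost list names experimental drugs and adverse-event treatment, but not expressly the replacement drugs taken after exit.

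**The case against.** The strongest reply is that the Per-Protocol Set is undefined and that a condensed article may leave its definition to the full protocol. Exit for relapse or intolerance is what the protocol itself directs, so such patients could count as protocol-compliant and stay in. Listing adverse-event treatment as a cost suggests that some do, and the decision tree in Fig. 2, which is not shown, may have branches for them. This stands in part: exclusion of adverse-event exits is possible, not established. It does not remove the point. A per-protocol set ordinarily excludes protocol violators, whom the article also says will be followed, and no all-randomised economic analysis is offered beside it.

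It is also fair that the primary comparison is untouched, that incremental cost per relapse avoided is a secondary outcome, and that the A versus B cost-effectiveness comparison is declared exploratory. That limits the consequence, but cost-effectiveness remains a named aim.

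Four stronger readings are tempting and not supported:

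- A reader might infer that all exited patients are discarded. Relapsers cannot be, as shown under the working.
- A reader might infer that the least tolerated group is bound to look cheaper and more effective. The direction cannot be determined: if excluded A patients relapse less often than those retained, A looks worse.
- A reader might take 20% of 240, that is 48 patients, as the number lost. The 20% is a dropout allowance for the sample size. The article does not link it to the Per-Protocol Set, and it is no upper bound on exclusions. Any figure for biologic use left out would likewise need invented exit rates, timings and later treatments; the article also allows csDMARD combinations after exit.
- A reader might infer that a change of wording is enough. Utilities and relapse status after exit are not clearly scheduled, so a missing-data method is needed too.

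**Conclusion.** The point holds. Resting both the economic base case and its sensitivity analysis on the Per-Protocol Set is a stated choice. It conflicts with the planned follow-up of early exits and protocol breaches, and with the intention-to-treat approach to relapse. The ICER can be distorted in either direction, and its effectiveness term need not match the primary result.

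The size is illustrative. It rests on the protocol's expected relapse rates, an assumed exclusion of 10% to 20% of group A, and exclusions in C unrelated to outcome. Under these, the effectiveness difference could fall anywhere from about half to about one and a half times its all-randomised value. The intention-to-treat relapse comparison of A with C is not affected.

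**What to change.** Make all randomised patients, analysed as allocated, the economic base case. Use the post-exit cost follow-up already planned, and state that treatment costs after exit are counted whatever the treatment received. State a method for relapse status and utilities missing after exit, for example multiple imputation within group. Keep the Per-Protocol Set as a sensitivity analysis only, with a definition that says how relapsers and adverse-event exits are handled.

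The cost is small: a change to the analysis text, some imputation work, and probably wider intervals for QALYs. No added patients are needed. The article reports the trial as ongoing with 123 patients in the randomised stage, so the change can be made before the database is locked.
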